## Assignment of interventions: Blinding

### Who will be blinded {17a}

Due to the nature of the study, it is not possible to blind at the practice level. Physicians will always be aware to which group they belong, as will the patients.

### Procedure for unblinding if needed {17b}

Not applicable: there is no blinding in this study.

## Data collection and management

### Plans for assessment and collection of outcomes {18a}

As stated above, to be able to track patients in the intervention group who were prescribed the FibriCheck® app, physicians will be asked to flag the specific patient file with a note saying “FC” or “FibriCheck,” or using the specific and personal ID created on the FibriCheck® app to link the app data to the patient file.

#### Data collected on demographics and clinical characteristics

To be able to compare both groups in terms of clinical similarity, we will provide relevant data that allows a reasonable comparison between the intervention and control groups. The data will be extracted from the medical software each practice uses by using the INTEGO procedures. The results will be analyzed and presented on the level of the practice. Baseline group characteristics relevant for the study will be assessed at the start of the study (Table 2).

**Table 2 Tab2:** Collected data on group characteristics (for control and intervention groups)

Group characteristics (***n*** = 22)	
Mean age Gender distribution Mean body mass index Mean systolic/diastolic blood pressure, heart rate Smoking status (current, former, never) Antihypertensive medication Type II diabetes Heart failure Myocardial infarction	

If not already present in the patient file, missing data will be collected during this first interview. For example, if there is no mention of a patient’s blood pressure or height and weight, the participating physician will measure these parameters and put them into the EHR.

The general group characteristics schematized in Table 2 will be used to calculate the cardiovascular CHARGE-AF risk score of patients in the intervention group.

### Plans to promote participant retention and complete follow-up {18b}

There will be no specific strategies or plans to promote participant retention, in addition to those mentioned above.

### Data management {19}

The data gathered during the study of the patients that are prescribed the FibriCheck® app will be collected on the FibriCheck® platform, a cloud-based storage space. The research team (headed by the authors of this protocol) will be given credentials to access this platform and extract the data for interpretation and analysis (in the .csv (comma-separated values) file format), as will authorized employees of Qompium, the general practitioners of the selected practices and a cardiologist specifically assigned to the study. Only the research team will perform the extraction and analysis of these data. Measurements of the app are color-coded, indicating normal versus aberrant heart rhythm and their likelihood (from green over orange to red), or measurement errors (blue, indicating insufficient signal quality for analysis).

After collection, the data will be pseudonymized before access is granted to the FibriCheck® platform.

### Confidentiality {27}

The study data will be stored on a secured central server, accessible only for Qompium employees and the study researchers, including the participating GPs and cardiologists. The data will be accessible for the entire study period, and for 3 years thereafter, or longer if Belgian law so requires.

Personal information will be pseudonymized, as outlined above. Every participant will receive an individual and unique code, but names or identifiable information will not be collected to create this code.

Study data will be shared with Qompium as they provide the server on which the data will be stored. Data will not be shared with other third parties, national nor international.

### Plans for collection, laboratory evaluation, and storage of biological specimens for genetic or molecular analysis in this trial/future use {33}

Not applicable, no biological specimens will be collected in this study.

## Statistical methods

### Statistical methods for primary and secondary outcomes {20a}

We will analyze our data on an intention-to-screen basis, evaluating the outcomes on the practice (cluster) level. There will be no subgroup analyses.

The intention-to-screen analysis means we will include all participants of both the control and intervention groups in the final analysis, regardless of whether they did receive the stated screening intervention or dropped out before they could do so. This ensures that no bias is introduced by looking at the data on the practice level, for example by erroneously overestimating the effect of the intervention (screening with FibriCheck® on top of standard screening). This approach is valid as long as the studied population is appropriately randomized [36].

We will analyze the results on the cluster level, as the study is also randomized at the cluster level. Statistical efficiency should be sufficient with the cluster sizes being equal, as outlined above. As the unit of inference will be the cluster, and not the participant, we will apply standard *t* tests with inverse-variance weighting [37]. Given the fact that we have two independent study populations, we will use the paired (independent samples) *t* test. Because the observations within each cluster will likely be correlated, it is essential to account for this correlation, by choosing an appropriate method of analysis. The small number of clusters in this study could lead to an inflation of the type I error when applying individual level analyses. Inverse-variance weighting is one cluster-level strategy to reduce the type I error while maintaining sufficient statistical power [37].

### Interim analyses {21b}

There will be no interim analyses.

### Methods for additional analyses (e.g., subgroup analyses) {20b}

There will be no subgroup or any additional analyses.

### Methods in analysis to handle protocol non-adherence and any statistical methods to handle missing data {20c}

For sample size calculation, we already assumed a loss to follow-up (LTFU) of 15%. The barrier to entry in this study is very low and takes place in the context of a normal doctor’s appointment. Also, results will be read from the practice level, so all information will be collected in a coded fashion and patient confidentiality will be automatically ensured. This will also be outlined in the patient study information leaflet. We anticipate that these factors will reduce LTFU as much as possible.

We will keep track of LTFU—for any reason—during the study and compare LTFU between control and intervention group at the end. Any significant difference will be discussed. Patients who do not complete the 4-week study period (for whatever reason), will not be included in the results.

For missing data, we will use multiple imputation to obtain complete datasets.

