### Eligibility criteria {10}

To be eligible for inclusion in the study, *practices* must conform to the following conditions:
It is a Flemish primary care practice in the INTEGO network.The practice uses an electronic health record (EHR), automatically linked to the INTEGO database.ECG devices used for diagnosis (i.e., confirmation of AF) must be 12-lead.The physician signs a specific study consent form.

To be eligible for inclusion in the control or intervention groups of the study, *patients* must conform to the following conditions:
The patient is 65 years or older.The patient has an electronic medical record (EMR) in the practice. This EMR contains all the patient information, for instance regarding medical history and medication, and is managed by the general practitioner.If the patient will be prescribed the FibriCheck® app, he/she signs the relevant patient consent form. Patients in the control group will also be required to sign a consent form.

Exclusion criteria for both the control and intervention group will be defined as follows:
The patient has already been diagnosed with AF.The patient is already under anticoagulant therapy.The patient has a pacemaker. Active pacing during measurements influences the results obtained with the FibriCheck® app [26].The patient is unable to use the FibriCheck® application independently due to cognitive disorders, functional limitations, visual impairments… These will be identified using diagnosis codes in the patient file.

Drop-out criteria for patients in the intervention group will be defined as follows:
Less than 20 measurements with the FibriCheck® app during the study period.Less than 2 measurements per day during the study period.On patient request, for whatever reason.

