### Criteria for discontinuing or modifying allocated interventions {11b}

A minimum of 20 measurements in total per patient in the intervention group is necessary to be considered for inclusion in the study. Patients will be expected to measure at least twice a day (morning and evening). The intervention will always be discontinued on patient request.

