##### Death

We will keep track of all-cause mortality during the study period, as well as the difference in mortality between control and intervention populations.

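### The plan promises to analyse every participant by intention to screen, yet it also excludes non-completers and, in the intervention arm only, patients with fewer than 20 measurements

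*Protocol article*

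**What the plan says.** The statistical methods section {20a} states the principle: "We will analyze our data on an intention-to-screen basis, evaluating the outcomes on the practice (cluster) level". It explains that "we will include all participants of both the control and intervention groups in the final analysis". Patients who were never screened or who left early are covered by this too, since everyone stays in "regardless of whether they did receive the stated screening intervention or dropped out before they could do so". The section gives avoidance of an overestimated effect as a reason.

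Other sections of the protocol article set different rules:

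- **Non-adherence and missing data {20c}, both arms:** "Patients who do not complete the 4-week study period (for whatever reason), will not be included in the results".
- **Criteria for discontinuing or modifying {11b}, intervention arm only:** "A minimum of 20 measurements in total per patient in the intervention group is necessary to be considered for inclusion in the study". The intervention description {11a} says the same.
- **Eligibility criteria {10}, drop-out criteria, intervention arm only:** a shortfall in the total, "Less than 20 measurements with the FibriCheck® app during the study period"; a shortfall in the daily number, "Less than 2 measurements per day during the study period"; or the patient's request. This section does not itself say that drop-outs leave the analysis.

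Mortality is a secondary outcome: "We will keep track of all-cause mortality during the study period", with a comparison between arms. Compliance is another secondary outcome, with the minimum number of measurements as its example. Section {20b} allows no subgroup or additional analyses.

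**The concern.** An analyst cannot both keep everyone who dropped out and remove everyone who did not finish. The primary estimate therefore depends on which section is followed. The trial is unblinded, so that choice could be made with the results in view, and {20b} leaves no room for a second analysis that would show how much it matters.

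The exclusions also undermine the comparison. They act on what patients do after allocation, and the 20-measurement rule can only remove patients from intervention practices. Controls have no app and no equivalent hurdle. The patients left in the two arms are then no longer those that randomization of practices made comparable, which is the condition {20a} sets for its own approach.

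Finally, the exclusions can remove outcome events. A patient who dies within the 4 weeks has not completed them. A patient whose AF is found early and who then stops measuring could fall below 20 measurements.

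**Working it through.** **1. The rules side by side**

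| Patient | {20a} | {20c} | {11a}, {11b} |
|---|---|---|---|
| Control, leaves before 4 weeks | kept | removed | no rule |
| Intervention, leaves before 4 weeks | kept | removed | removed if under 20 measurements |
| Intervention, completes 4 weeks, under 20 measurements | kept | kept | removed |
| Either arm, dies within 4 weeks | kept | removed | intervention: removed if under 20 measurements |

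The last column reads inclusion in the study as covering the results. No row gives the same answer throughout.

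**2. The plan's own sample size**

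Inputs from Sample size {14}: control rate 13.65 per 1000, two-sided α 0.05, power 0.80, ICC 0.0027, 400 patients per practice, 15% loss to follow-up. The 2-fold effect comes from Outcomes {12}.

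- Rates 0.01365 and 0.02730, two-proportion formula with continuity correction: 1833 per arm, against 1835 stated.
- Design effect: 1 + 0.0027 × 399 = 2.077. Then 1835 × 2.077 = 3811 per arm.
- Total: 2 × 3811 × 1.15 = 8765.

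The stated size therefore reproduces with the 2-fold effect, which is used below. The 24.57 per 1000 in {14} does not reproduce 1835, either as a rate (2467, or 2647 with correction) or as an increase (656 or 735).

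**3. Bias from dropping patients in one arm, with no true effect**

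Let *f* be the fraction of the intervention arm dropped and *r* the AF rate in dropped patients divided by that in retained patients. The observed ratio to control is 1 / ((1 − *f*) + *f* × *r*). Neither *f* nor *r* is in the documents. As an assumption, take *f* = 0.15, borrowing the size of the loss-to-follow-up allowance:

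- *r* = 0: 1 / 0.85 = 1.18
- *r* = 0.5: 1 / 0.925 = 1.08
- *r* = 1: 1 / 1 = 1.00
- *r* = 2: 1 / 1.15 = 0.87

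**4. Bias when the intervention works**

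Assume a true intention-to-screen ratio of 2.0 and non-compliers at the control rate. Dropping them gives (2 − *f*) / (1 − *f*): 2.05, 2.18 or 2.43 for *f* = 5%, 15% or 30%.

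**5. The measurement thresholds**

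Two a day for 28 days is 56. Twenty measurements at two a day take 10 days. A patient who measures as asked for 10 days and then stops meets the total but not the daily criterion.

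**6. Power if everyone is kept**

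If the 2-fold effect applies to compliers and non-compliers have the control rate, the intention-to-screen ratio is 2 − *f*.

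| *f* | Ratio | Power at 1835 per arm |
|---|---|---|
| 5% | 1.95 | 0.76 |
| 15% | 1.85 | 0.68 |
| 30% | 1.70 | 0.53 |

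This uses the continuity-corrected formula, with 1835 as the size per arm after dividing out the design effect. Keeping patients whom the 15% allowance expected to lose gives some power back. The full enrolment corresponds to 8765 / 2 / 2.077 = 2110 per arm, where power at *f* = 15% is 0.74.

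**The case against.** The best defence is that the eligibility section only labels patients as drop-outs, and {20a} keeps drop-outs, so those two sections agree. The minimum number of measurements is also named as a compliance outcome, and {11a} and {11b} speak of inclusion in the study rather than in the analysis. The point about {10} stands: that section alone removes nobody from the results. It does not rescue {20c}, which speaks of the results directly, nor a condition of inclusion that can only be judged after the patient has been enrolled and followed.

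Several stronger readings are tempting, but the documents do not support them.

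- **That the detection rate is inflated.** With 30% dropped and no AF among them, the ratio under no effect would be 1 / 0.70 = 1.43. Neither input is in the documents. Intervention patients also receive opportunistic screening, so some AF would be expected among those dropped. Losing early-diagnosed cases would push the ratio the other way.
- **That almost everyone is excluded.** If one missed measurement removed a patient, 95% or 99% adherence per measurement would leave 0.95^56 = 6% or 0.99^56 = 57%. This assumes independent misses and no credit for extra measurements, and it would make the floor of 20 pointless. A floor of 20 and a frequency of two a day can both be met, so the fault is unclear wording, not a numerical contradiction.
- **That no deaths can be counted.** This holds only within a patient's own 4 weeks. The article also calls the 12 months the study period, and later deaths could be counted on that reading.
- **That the stroke comparison is invalid.** A patient can have a stroke or TIA and still complete 4 weeks, so the counts may be truncated but are not emptied.
- **That detected AF is certainly lost.** The article does not say that measuring stops at diagnosis. It also makes no exception for diagnosed patients.
- **That multiple imputation is left with nothing to do.** It may serve missing baseline and CHARGE-AF data, so no error is shown there.

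**Conclusion.** The point holds and must be fixed. The article sets incompatible analysis populations for its primary outcome: everyone under {20a}, and completers with at least 20 measurements in the intervention arm under {20c}, {11a} and {11b}. The contradiction needs no assumption; it is on the face of the text.

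The direction of the bias is not established. Under the assumption of 15% dropped from the intervention arm and no true effect, the ratio runs from 0.87 to 1.18 over the values of *r* tried. Because the sign is unknown, the bias could not be allowed for when the results are interpreted.

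Literal application also removes deaths within a patient's 4 weeks from the mortality comparison. Loss of some early-diagnosed AF, which would also distort the average time to detection, is possible but remains an inference.

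**What to change.** 1. In {20c}, delete the sentence that leaves non-completers out of the results.
2. In {11a} and {11b}, delete the wording that makes 20 measurements a condition of inclusion.
3. State that all enrolled patients are analysed in the arm of their practice. Count AF, stroke or TIA, and death regardless of app use or completion, up to withdrawal of consent where that ends use of the data.
4. Reconcile the total and daily thresholds in {10}, and use them only to define the compliance outcome.
5. If a per-protocol analysis is wanted, label it supportive and amend {20b}, which currently rules out additional analyses.

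**Cost.** This is mainly wording, and the article says recruitment had not started. INTEGO collects diagnoses automatically, but the article does not list death among its items, so the source for deaths should be confirmed. Non-compliers may dilute the detection rate. The plan should therefore say whether the 2-fold effect refers to compliers or to all enrolled patients and, if to compliers, restate the power: about 0.68 at 15% non-compliance on the planned evaluable size, under the assumptions above.

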## Methods: Participants, interventions, and outcomes

### Study setting {9}

This study will take place in the eligible Flemish primary care practices in the INTEGO network.

The INTEGO network is a morbidity registry containing coded contents of the electronic health records of some 400,000 patients from 100 general practitioner’s offices all over Flanders. The information is automatically collected during daily practice and contains diagnoses, year of birth, gender, prescriptions, lab results, and various biomedical parameters such as blood pressure, height, weight, etc. [1]. The INTEGO procedures have been validated by the Belgian Privacy Commission. The registry is hosted on the Healthdata platform (www.healthdata.be) [28].

Patients coming to the eligible practices, as well as the practices themselves, will be recruited separately. They will fill in separate consent forms. After consent is given by the patient, the GPs of the recruited practices will explain the study outline and specific details, such as the installation and use of the app, at the first consultation, after which the study period for that specific patient will commence. General care will proceed as normal.

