### Outcomes {12}

#### Primary outcome measures

##### Detection rate of AF in patients 65 years and older

The detection rate of AF in both the control and intervention group will be calculated after 4 weeks. A significant difference in both groups will be noted. Compared with previous studies of similar design [32–34], we will realistically assume a 2-fold increase in the detection rate of AF in the intervention group to be significant.

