##### Average time to detection of AF

We will compare the average time from the beginning of the study to the primary endpoint, the diagnosis of AF, in both study arms.

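### The missing-data rules in {20c} do not fit a detection outcome analysed by intention-to-screen: drop-outs are to be included, excluded and possibly imputed, and an imputed positive would be AF that nobody detected

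*Protocol article*

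**What the plan says.** Three statements bear on patients who stop early.

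- **Include.** Statistical methods {20a} sets an intention-to-screen analysis of all participants, "regardless of whether they did receive the stated screening intervention or dropped out before they could do so".
- **Exclude.** Section {20c} says: "Patients who do not complete the 4-week study period (for whatever reason), will not be included in the results". The sample size section {14} fits this, since it inflates the number for 15% loss to follow-up.
- **Impute.** The next sentence in {20c} is: "For missing data, we will use multiple imputation to obtain complete datasets". It names no variable and exempts none.

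The outcome and test are these. Under Outcomes {12}: "The detection rate of AF in both the control and intervention group will be calculated after 4 weeks". Under {20a}: "we will apply standard *t* tests with inverse-variance weighting", with no covariate named. Section {20b} rules out any additional analysis. A second outcome listed as primary rests on the same event: "We will compare the average time from the beginning of the study to the primary endpoint, the diagnosis of AF, in both study arms".

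On the data source, Eligibility criteria {10} requires: "The practice uses an electronic health record (EHR), automatically linked to the INTEGO database". Study setting {9} says of the registry: "The information is automatically collected during daily practice and contains diagnoses". Section {18a} has missing baseline items measured at the first interview.

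Eligibility criteria {10} also classes intervention patients as drop-outs if they make too few app measurements. No matching criterion exists for control patients.

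**The concern.** Detection is an event in the patient's record: within the window a confirmed AF diagnosis was made, or it was not. A patient who stops using the app but still has a linked record normally has a known value, namely not detected. That is a true result of the screening strategy, and intention-to-screen exists to count it.

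Both rules in {20c} work against this. Exclusion removes the patients in whom the app strategy failed to take hold. Imputation within arm, if applied to detection, would give those patients the detection rate of those who kept measuring. Either way the estimate moves from the yield of offering the app towards the yield among people who use it. Because under-use of the app can make a patient a drop-out in one arm only, the two arms need not be affected equally.

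An analyst could also keep, drop or impute these patients and cite the protocol for each choice. In an unblinded trial that choice should be closed before data are seen.

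**Working it through.** **1. The plan's own figures.** Inputs from {14}: control rate 13.65 per 1000, power 0.80, two-sided α 0.05, ICC 0.0027, 400 patients per practice, 15% loss. From {12}: a 2-fold effect, so 27.30 per 1000.

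- Two-proportion formula: 1689 per arm. With continuity correction, n/4 × [1 + √(1 + 4/(nΔ))]² with Δ = 0.01365 gives 1833, against the stated 1835.
- Design effect: 1 + 0.0027 × 399 = 2.077; 1835 × 2.077 = 3811 per arm.
- Loss: 3811 × 2 × 1.15 = 8765 in total, about 4382 per arm. 15% of that is about 657 patients per arm.

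The figure of 24.57 per 1000 in {14} is worded there as an absolute increase, but 24.57/13.65 = 1.8, so it looks like an intervention rate. As a rate it needs 2467 per arm (2647 with correction), and as an increase (38.22) it needs 656 (735); neither gives 1835. Both 24.57 and 27.30 are carried below as intervention rates.

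**2. What could be imputed.** The detection test uses arm, practice and AF status. Arm and practice are known. Baseline characteristics do not enter it. For this test, imputation acts on AF status or on nothing.

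**3. Effect on the arm difference.** Let d be the drop-out fraction in each arm, p_I and p_C the detection rates of completers, and r_I and r_C the recorded detection rates of drop-outs.

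- By recorded status: D = (1−d)(p_I − p_C) + d(r_I − r_C)
- Drop-outs excluded, or imputed within arm (expected value): D* = p_I − p_C

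If r_I = r_C, then D*/D = 1/(1−d), an overstatement of d/(1−d), whatever the rates: 5% at d = 0.05, 18% at 0.15, 33% at 0.25.

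With d = 0.15, per 1000 (D* is 10.92 for p_I = 24.57 and 13.65 for p_I = 27.30):

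| Drop-outs, app arm / control arm (assumed) | D, p_I = 24.57 | D* against D | D, p_I = 27.30 | D* against D |
|---|---|---|---|---|
| control rate / control rate | 9.28 | +18% | 11.60 | +18% |
| none / none | 9.28 | +18% | 11.60 | +18% |
| none / control rate | 7.23 | +51% | 9.56 | +43% |
| control rate / none | 11.33 | −4% | 13.65 | 0% |
| own arm's rate / own arm's rate | 10.92 | 0% | 13.65 | 0% |
| app-arm rate / none | 12.97 | −16% | 15.70 | −13% |

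First row in full: 0.85 × 10.92 = 9.28, and 10.92/9.28 = 1.18.

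**4. In cases.** With p_I = 24.57 and 657 drop-outs per arm, imputing detection would add 657 × (24.57 − 13.65)/1000 ≈ 7 undetected AF cases to the app arm if its drop-outs are in truth detected at the control rate, and 657 × 24.57/1000 ≈ 16 if none is. In the control arm it would add 0 to about 9 (657 × 13.65/1000).

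The rates in {14} are annual, while the outcome is read at 4 weeks. The absolute figures are therefore illustrative. The ratio in the equal-rates rows depends on d alone.

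**The case against.** The strongest reply is that the protocol never says AF detection will be imputed. Which variables are imputed, and with what model, can properly wait for the analysis plan, and imputation has a plausible use for the baseline table and the CHARGE-AF inputs. The preceding sentence in {20c} excludes non-completers, so on its face the 15% lost would be dropped and not imputed. All of this stands.

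A reader might infer more than the documents support:

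- **That the registry holds AF status for every enrolled patient.** Linked records make this likely, but no section states it, and the Discussion treats complete coding by physicians as a risk. If it were fully true, imputation would have nothing to fill.
- **That the bias must favour the app.** Imputation and exclusion would apply to both arms. The table has rows with no distortion and rows where the effect is understated.
- **That the 18% is caused by imputation.** Exclusion, which the protocol does state, gives the same expected difference. The figure belongs to both rules.

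What the reply does not remove is the contradiction between {20a} and {20c}. That is written in the protocol and is not a detail left to the analysis plan. Nor does it supply any variable other than detection on which imputation could act in the primary test. The understating rows also need app-arm drop-outs to be detected more often than control drop-outs. Both arms receive the same opportunistic screening, so equal rates are the more natural assumption, though still an assumption.

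**Conclusion.** The point holds as an inconsistency with a plausible but uncertain bias. Sections {20a} and {20c} give incompatible instructions for drop-outs, and neither exclusion nor imputation suits an outcome for which an undiagnosed patient with a linked record counts as not detected.

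If drop-outs in both arms are detected at the same rate, exclusion or within-arm imputation overstates the arm difference by d/(1−d), about 18% at 15% loss. Over the assumptions tried, the error runs from about +51% to −16%. The documents give no detection rates for drop-outs, so neither sign nor size is established. The result also assumes equal loss in the two arms. No conclusion is drawn that the trial will impute AF detection.

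**What to change.** Replace both the exclusion sentence and the imputation sentence in {20c} with:

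> Every enrolled patient is analysed in the arm of their practice. AF status is taken from the EHR/INTEGO record over the 4-week outcome window; no confirmed AF diagnosis counts as not detected, whatever the number of app measurements. AF detection is not imputed; multiple imputation, if used, is limited to baseline characteristics. Patients whose record left the network are reported by arm, with a sensitivity analysis.

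Amend {20b}, which now forbids any additional analysis, to allow that sensitivity analysis. For consistency, state that the measurement thresholds in {10}, {11a} and {11b} describe compliance and do not define the analysis set.

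The cost is a wording change and one small extra analysis; no new data are collected. The downside is that the estimate may become slightly less favourable to the app, because patients who were offered it and stopped now count. The result still depends on complete coding of diagnoses, which the protocol already recognises as a risk.
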